#### Objective 2 and 3a

Literature on patient satisfaction in South Africa is scarce; in other studies, patient satisfaction varies from <50% to as high as 75% [25]. The impact of the intervention on patient satisfaction may likely be less compared with that before the COVID-19 era because of disruptions in service delivery. For the 18 facilities in the intervention arm and 18 facilities in the control arm, at a power of 80%, and an expected increase in patient satisfaction from 50% to 60%, given an intraclass correlation coefficient of 0.06, the number of pregnant women required is 102, with a total sample size of 1529 per arm in the pre- and postintervention periods.

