### Eligibility Criteria and Recruitment of Facilities

#### Overview

The intervention facilities were purposively identified by the National Department of Health (NDOH) as sites with MNH service performance and capacity below the national average in South Africa. In addition, the selected intervention sites reflect the clinical and referral pathways and represent both urban and rural settings. For objectives 2 and 3, the comparison districts were purposively selected to match the intervention districts in as many respects as possible, including iMMR, stillbirth rate, neonatal mortality rate, sociodemographic characteristics, service organization, and setting (rural, urban, and periurban), and to provide the NDOH standard of care. In total, 3 facilities (2 district hospitals and 1 regional hospital) in the comparison district were selected and matched to the intervention district based on the total number of births. Data collection for objectives 2 and 3 is conducted in 18 hospitals (15 district- and 3 regional-level hospitals). Objective 4b is being conducted in 15 hospitals, purposively selected from the 21 intervention facilities.

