### Sample Size

#### Objective 1

Using the number of deliveries and maternal and perinatal deaths in 9 regional and district facilities in the chosen intervention catchment areas (the Eastern Cape, Limpopo, and Mpumalanga) between 2018 and April 2019, rates were found to be 115.4 maternal deaths per 100,000 live births, 14.4 neonatal deaths per 1000 live births, and 22.5 stillbirth births per 1000 facility births. For this study, an intraclass correlation estimator from a random intercept logistic regression model was used. Using the average facility size (based on deliveries in the intervention catchment areas during the baseline period), the variance inflation factor was estimated at 1.0, 1.4, and 1.3 for the maternal mortality ratio, neonatal mortality rate, and stillbirth rate, respectively. To test the hypothesis that there was no improvement against a 50% increase in the baseline, with 80% power at a 5% two-sided significance level, the number of live births would be 40,524 and 4512 for testing maternal and neonatal mortality rates and 2666 for stillbirth rates. We will observe at least 41,000 deliveries pooled across the 3 catchment areas over a 3-year period to have minimum power for all outcome comparisons. The same would accrue in the control facilities.

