#### Objective 3b

The study team will evaluate 18 facilities (3 in each of the intervention and control catchment areas).

#### Objective 4

Sampling at the meso- and macrolevels will be linked to the microlevel sampling. The subdistricts and districts where facilities have been selected and their respective area levels will be included in the evaluation at the macro- and mesolevels. At minimum, 2 subdistricts, 2 districts, and 3 areas (total 7 “units” of assessment) will be selected, although additional units could be added if primary health care clinics, community health care centers, and district hospitals are not all from the same subdistrict. We anticipate approximately 90 and 120 interviews or FGDs, respectively, for the macro-, meso-, and microlevel interviews or FGDs over the 18 months of data collection. At the microlevel, we sampled QI teams across the 3 catchment areas, as follows:

Objective 4b facilities (Table 2) were sampled based on readiness assessment scores from the NDOH (this was done before the start of the intervention to assess the state of maternal and neonatal care in the intervention facilities) and input from the QI advisers and represent the range of facility types; MNH care packages; and urban, semiurban, and rural areas.

**Table 2 table2:** Type of objective 4b facilities sampled in Eastern Cape, Limpopo, and Mpumalanga from 2020 to 2022 (N=15).

	Eastern Cape (n=4), n (%)	Limpopo (n=5), n (%)	Mpumalanga (n=6), n (%)
Regional hospital (n=3)	1 (7)	1 (7)	1 (7)
District hospital (n=4)	1 (7)	1 (7)	2 (13)
Community health care center (n=5)	1 (7)	2 (13)	2 (13)
Primary health care clinic (n=3)	1 (7)	1 (7)	1 (7)

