### Maternal Satisfaction With Care

From October 27, 2021, to July 8, 2022, there were 3934 completed maternal interviews across 18 hospitals. In the maternal interviews, participants were largely satisfied with their antepartum care (3556/3841, 92.58%). Approximately 5.88% (226/3841) of the participants self-reported complicated deliveries.

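### The objective 2/3a sample size assumes 18 facilities per arm when the study has 18 hospitals in total, and its printed figures do not give 80% power

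*Protocol article*

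**What the plan says.** The paragraph Sample Size, Objective 2 and 3a plans for a rise in satisfaction from 50% to 60% with an ICC of 0.06. Its facility count and power are: "For the 18 facilities in the intervention arm and 18 facilities in the control arm, at a power of 80"%. It concludes that "the number of pregnant women required is 102, with a total sample size of 1529 per arm", and refers this to the periods before and after the intervention. It gives no significance level.

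Three other places give a different number of facilities:

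- Eligibility Criteria and Recruitment of Facilities, Overview: "Data collection for objectives 2 and 3 is conducted in 18 hospitals (15 district- and 3 regional-level hospitals").
- Sample Size, Objective 3b: "The study team will evaluate 18 facilities (3 in each of the intervention and control catchment areas").
- Results, Maternal Satisfaction With Care: "there were 3934 completed maternal interviews across 18 hospitals".

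Sample Size, Objective 1 draws its baseline rates from "9 regional and district facilities in the chosen intervention catchment areas", which agrees with 9 hospitals in the intervention arm.

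**The concern.** The study total of 18 appears to have been entered as the number in each arm. In a clustered comparison the number of hospitals limits power far more than the number of women does, so doubling the hospitals on paper changes the power materially. The paragraph's own numbers also do not fit together, so correcting the count alone would not rescue the stated 80%.

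Patient experience and quality of maternal care are named secondary end points. A reader who relies on 80% power could take a null difference in satisfaction between arms as evidence of no effect, when the study would more likely than not have missed the planned 10-point effect.

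**Working it through.** **Inputs.** From Sample Size, Objective 2 and 3a: p1 = 0.50, p2 = 0.60, ICC = 0.06, 80% power, 18 facilities per arm, 102 women (read as per facility) and 1529 per arm. From the facility descriptions: 18 hospitals in total, and 3 in each of three areas per arm = 9 per arm (explicit for objective 3b, inferred for 2 and 3a). Assumed: two-sided 5%, as stated for objective 1. Hospitals are treated as equal in size.

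**Step 1: trying to reproduce the printed figures.**

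Without clustering, n per arm = [1.96 x sqrt(2 x 0.55 x 0.45) + 0.842 x sqrt(0.25 + 0.24)]^2 / 0.10^2 = 387.3, rounded up to 388.

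- 18 x 102 = 1836, which is not 1529.
- 1529 / 102 = 15.0, so 102 fits 15 facilities per arm, not 18 (1529 / 18 = 85) or 9 (1529 / 9 = 170).
- The design effect is 1 + (m - 1) x 0.06. With m = 50 it is 3.94, and 388 x 3.94 = 1528.7. This gives 1529 at the stated ICC, but a cluster size of 50 is stated nowhere and would need 1529 / 50 = 30.6, so 31 facilities per arm.
- With m = 102 the design effect is 7.06 and the requirement is 388 x 7.06 = 2739 women per arm, in 27 facilities.

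**Step 2: the limit set by the number of facilities.**

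With k facilities of m women per arm, the effective sample size is k x m / [1 + (m - 1) x 0.06]. As m grows this approaches k / 0.06. Reaching 388 needs k > 388 x 0.06 = 23.3, so at least 24 facilities per arm even with unlimited women. Both 18 and 9 fall short.

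**Step 3: power for a one-period comparison of arms.**

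Power uses the two-proportion normal formula at the effective sample size. The last column uses a noncentral t with 2k - 2 df.

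| Facilities per arm | Women per facility | Effective n per arm | Power (normal) | Power (t) |
|---|---|---|---|---|
| 18 | 85 (1529 per arm) | 253 | 62% | 60% |
| 18 | 102 | 260 | 63% | 61% |
| 18 | unlimited | 300 | 69% (70% unpooled) | 67% |
| 9 | 102 | 130 | 37% | 33% |
| 9 | 170 (1529 per arm) | 137 | 38% | 35% |
| 9 | 219 (3934 / 18) | 140 | 39% | 36% |
| 9 | unlimited | 150 | 41% (42% unpooled) | 38% |

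With one-sided 5%, the 9-per-arm rows for 102 to 219 women give 49-51%, with a ceiling of 54%.

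**Step 4: detectable difference with 9 per arm and 219 women each.**

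The standard error near 50% against 66% is sqrt[(0.25 + 0.22) / 140] = 0.058. Then (1.96 + 0.84) x 0.058 = 0.16, or about 16 points from 50%.

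**Step 5: a before-after comparison.**

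For difference-in-differences, let c be the correlation between a hospital's two period effects (an assumption; the article gives none) and s2 = (3 x 0.25 + 0.24) / 4 = 0.2475. The variance is 2 x [2 x 0.06 x (1 - c) x s2 / k + 2 x s2 x 0.94 / (k x m)]. With k = 9, m = 170 per period and c = 0.9 this is 2 x (0.00033 + 0.00030) = 0.00127. The standard error is 0.0356 and power is Phi(0.10 / 0.0356 - 1.96) = 80%. With c = 0.8 power is 62%, and with c = 0.7 it is 50%.

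**The case against.** The strongest reply is that the study is a controlled before-and-after design and that the paragraph sizes both periods. In such a comparison the stable differences between hospitals cancel, and the ceiling in Step 2 no longer applies. This stands as far as it goes. A reader might infer from Step 2 that no number of interviews could ever give 80%, and the documents do not support that beyond a one-period comparison of arms. But the before-after route needs a between-period correlation of about 0.9, which is not stated. Study Design and the Results place the objective 2 data in 2021-2022, after the intervention began, so the article describes no pre-intervention round to compare with.

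Four further points limit the concern:

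- **ICC.** A reader might infer that a smaller ICC than 0.06 was used. It need not have been: 1529 follows from 0.06 with a cluster size of 50.
- **Observed satisfaction.** The Results report that "participants were largely satisfied with their antepartum care (3556/3841, 92.58"%). A reader might infer that a 10-point rise was impossible and the 50% planning rate an error. That figure is for antepartum care only, is pooled over arms and was collected after the intervention began. It is neither a baseline nor a control rate, and a planning value is not made wrong by later data.
- **Objective 3a.** Its outcome is a percentage care score, so these binary power figures do not carry over to it.
- **Planned analysis.** The Objective 2 analysis is descriptive and exploratory and names no test between arms, although Table 1 speaks of an intervention effect over time. The risk of misreading a null result is therefore conditional on such a comparison being made.

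**Conclusion.** Wrong as written. The facility count in the calculation contradicts the rest of the article, the numbers 18, 102 and 1529 do not agree with each other, and the stated inputs do not give 80% power. For binary satisfaction compared between arms in one period, power is about 62-63% with 18 facilities per arm (ceiling about 70%). It is about 37-39% with 9 per arm (33-36% with t on 16 df; ceiling about 42%), roughly half the stated value.

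This rests on two-sided 5% borrowed from objective 1, equal hospital sizes, 102 read as women per facility, and the 9/9 split carried over from objective 3b. The contradiction in the count and the internal disagreement of the figures need only the last two readings at most, and one-sided testing does not restore 80%. The conclusion is confined to the one-period comparison of satisfaction.

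**What to change.** In Sample Size, Objective 2 and 3a:

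1. Correct the facility count to 18 hospitals in total, 9 per arm, and confirm that split for objectives 2 and 3a.
2. Reconcile 102 and 1529 with a stated cluster size and number of facilities, or remove them.
3. Name the comparison and the significance level, and replace the 80% claim with the power or detectable difference for that comparison. For one-period binary satisfaction this is about 37-39% power for 50% against 60%, or a detectable difference of about 16 points from 50%. If a before-after comparison is meant, state the between-period correlation and identify the pre-intervention data.
4. Say that the calculation covers binary satisfaction and not the objective 3a care score.
5. Report any between-arm difference as an estimate with a confidence interval that allows for clustering by hospital, so that a null result is not read as no effect.

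The interviews are complete, so the new figures should be labelled as a restatement for the design as run. The cost is a change of wording and a less favourable stated power; no new data are needed.

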#### Objective 3b

The study team will evaluate 18 facilities (3 in each of the intervention and control catchment areas).

#### Objective 4

Sampling at the meso- and macrolevels will be linked to the microlevel sampling. The subdistricts and districts where facilities have been selected and their respective area levels will be included in the evaluation at the macro- and mesolevels. At minimum, 2 subdistricts, 2 districts, and 3 areas (total 7 “units” of assessment) will be selected, although additional units could be added if primary health care clinics, community health care centers, and district hospitals are not all from the same subdistrict. We anticipate approximately 90 and 120 interviews or FGDs, respectively, for the macro-, meso-, and microlevel interviews or FGDs over the 18 months of data collection. At the microlevel, we sampled QI teams across the 3 catchment areas, as follows:

Objective 4b facilities (Table 2) were sampled based on readiness assessment scores from the NDOH (this was done before the start of the intervention to assess the state of maternal and neonatal care in the intervention facilities) and input from the QI advisers and represent the range of facility types; MNH care packages; and urban, semiurban, and rural areas.

**Table 2 table2:** Type of objective 4b facilities sampled in Eastern Cape, Limpopo, and Mpumalanga from 2020 to 2022 (N=15).

	Eastern Cape (n=4), n (%)	Limpopo (n=5), n (%)	Mpumalanga (n=6), n (%)
Regional hospital (n=3)	1 (7)	1 (7)	1 (7)
District hospital (n=4)	1 (7)	1 (7)	2 (13)
Community health care center (n=5)	1 (7)	2 (13)	2 (13)
Primary health care clinic (n=3)	1 (7)	1 (7)	1 (7)

### Intervention Dose

The intervention dose, defined as the “quality and quantity of an intervention and participation” [26], may be necessary to determine the barriers or enablers of the Mphatlalatsane Initiative. However, measuring the intervention dose is complex and requires substantial data collection to quantify the various intervention dose dimensions. Moreover, there are currently no accepted methods for measuring this dose. McHugh et al [26] outlines 8 dimensions of intervention dose that may affect whether or not a QI initiative succeeds. In the Mphatlalatsane Initiative, the measurement of the intervention dose is further complicated by the COVID-19 pandemic. The implementation of the Mphatlalatsane Initiative was ongoing for approximately 6 months when the first case of COVID-19 was diagnosed in South Africa in March 2020 [27]. Following the national state of the disaster and level-5 lockdown, the Mphatlalatsane Initiative was redefined to provide support to the intervention sites. This support took the form of a web-based platform, telephonic meetings, and in-person QI adviser support when lockdown restrictions eased. However, the use of the web-based platform to provide support was unsuccessful owing to issues with internet connectivity, the lack of equipment, and user competence. As such, the Mphatlalatsane Initiative implementation may have varied at the micro-, meso-, and macrolevels. To determine the Mphatlalatsane intervention dose at the microlevel, a scoring system is in development based on prior work [26]. The first 2 domains, exposure and intensity, relate to the QI adviser. *Exposure* is the number of interactions between the adviser and the QI team; *intensity* is the nature of the interaction between QI advisers and QI teams, for instance, face-to-face support to the team in reviewing their change ideas and offering technical advice during the support visit (high intensity) or a mobile call from the adviser to find out when the team will send their QI documentation (low intensity). The remaining 4 domains relate to the adopted change idea. Quantity is the number of adopted (ie, change ideas with quantifiable evidence that it improves care) change ideas; *reach* is the number of facility workers involved; *duration* is the implementation period in months; *scope* is the 5 Mphatlalatsane outcomes that have been targeted for the change ideas in terms of leadership, clinical care, health systems, patients’ experience of care, and patients’ health. For the period from September 2019 to December 31, 2021, retrospective data are collected by QI advisers for 4 domains: quantity, reach, duration, and scope (Multimedia Appendix 2). For the period from January 1 to December 31, 2022, all domains will be extracted from the adviser’s routine reports (Multimedia Appendix 2). The scoring of each domain and assessment of the intervention dose are evolving and will be finalized once the data have been collected. It is envisaged that 2 members of the evaluation team will independently score each domain, and disagreements will be resolved by a third member.

### Statistical Analysis

#### Objective 1

The institution maternal and perinatal mortality indicators will be calculated using DHIS data. Trend in iMMR, neonatal mortality rate, and stillbirth rates (with SE bars) during the pre- and postintervention periods will be disaggregated by intervention arms. RR and 95% CI will be calculated along with data on confounding variables, such as antenatal care coverage before 20 weeks, delivery at health facility access by tar road, deliveries of female participants aged <19 years, and deliveries of female participants aged ≥19 years (derived from total deliveries and deliveries of female participants aged <19 years). The trends in mortality and stillbirths will be compared before the COVID-19 pandemic (January 2019-March 2020) and during the COVID-19 pandemic (April 2020-March 2021) and in the context of the COVID-19 waves. The baseline period (2017-2018) will also be provided. Observed numbers and rates will be determined monthly and quarterly across all 9 provinces in the country and overall. To compare the Mphatlalatsane Initiative intervention and control arm trends in mortality, an interrupted time series regression model using Poisson regression model with Newey-West SEs to account for autocorrelation and possible heteroskedasticity will be used.

#### Objective 2

This study will use quantitative descriptive analyses and exploratory factor analysis to examine associations between sociodemographic characteristics, childbirth characteristics, and maternal participants’ experience of health care quality and the health care facility during the antenatal to postpartum period.

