### Study Design

We are conducting a mixed methods implementation science type 2 hybrid effectiveness design to study the intervention effect (objectives 1-3) and implementation (objective 4) during the COVID-19 pandemic. Given that the intervention facilities were preselected, the quantitative component will be implemented as a quasi-experimental controlled before-and-after study (nonrandomized assignment of the intervention and comparison groups) to measure the effect of a QI intervention implemented during the COVID-19 pandemic on maternal and neonatal outcomes. Data on the iMMR, neonatal mortality rate, and stillbirth rate will be analyzed from 2019 to 2021, including the time before and during the COVID-19 pandemic in South Africa (objective 1). Study data on maternal experiences of care (objective 2) and maternal and neonatal quality of care (objectives 3a and 3b) were collected between 2021 and 2022. Objective 4 data collection commenced in early 2020 and ended in August 2022.

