### Data Sources

#### Objective 1

Mortality data from 2017 to 2022 were extracted from the District Health Information System (DHIS; Table 1).

**Table 1 table1:** Mphatlalatsane data sources.

Objective	Data source	Variable or theme	Level of analysis
1	DHIS^a^	Mortality data (maternal, neonatal, and stillbirths) extracted quarterly from 2019 to 2022	District and facility
2	Participant interview shortly after delivery in regional or district hospitals	The effect of the QI^b^ intervention over time on patients’ experience of the quality of antenatal and postnatal health care services from 2021 to 2022	Individual
3a	Maternal records from regional or district hospitals	Facility audit of maternal records will be conducted to measure adherence to clinical protocols on normal pregnancy, HIV, eclampsia, and postpartum hemorrhage from 2021 to 2022	Individual
3b	Structured observation checklists will be interviewer administered in selected facilities based on the Newborn QI Toolkit norms and standards for newborn care, which were developed to collect data in each facility [23]	Availability of equipment and supplies Availability of guidelines or policies Distribution and availability of drugs Data quality and use Staffing Infrastructure	Facility
4a	Semistructured interviews and FGDs^c^ with the QI advisers, operational managers, and management staff	Stakeholder analysis: coordination processes, nature and quality of social networks, decision-making processes, formal and informal communication, and collaboration between key actors. We will set up monthly individually open-ended debriefing meetings with the QI advisers, and they will reflect on their work and engagement with the QI teams. We will also review program documentation, including the documentation that the QI teams will generate during the PDSA^d^ cycles. We will also conduct other program meetings at the macro- and mesolevels.	National, provincial, district and subdistrict

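### The 2019-2021 window stated for objective 1 leaves only 8 to 11 pre-intervention months for the interrupted time series, and the data windows and start dates conflict

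*Protocol article*

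**What the plan says.** The article gives several time frames for the primary mortality endpoints.

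- **Analysis window.** Study Design: the rates "will be analyzed from 2019 to 2021, including the time before and during the COVID-19 pandemic in South Africa (objective 1").
- **Data held.** Data Sources, Objective 1: "Mortality data from 2017 to 2022 were extracted from the District Health Information System". Table 1 in the same section instead gives a quarterly extraction covering 2019 to 2022.
- **Earlier years.** Statistical Analysis, Objective 1: "The baseline period (2017-2018) will also be provided". It does not say whether these years enter the model.
- **Dated split.** The same section compares trends "before the COVID-19 pandemic (January 2019-March 2020) and during the COVID-19 pandemic (April 2020-March 2021").
- **Arm comparison.** That section separately promises trends by arm over pre- and postintervention periods, which it does not date. It names an interrupted time series Poisson model with Newey-West standard errors, without a date for the interruption or a length for the series.
- **Start of the intervention.** Intervention Dose: the Initiative had been "ongoing for approximately 6 months when the first case of COVID-19 was diagnosed in South Africa in March 2020". Dose recording starts in the same month: "For the period from September 2019 to December 31, 2021, retrospective data are collected by QI advisers for 4 domains". The Discussion repeats the 6 months. The Abstract places the start at the end of 2019.

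**The concern.** An interrupted time series estimates the intervention effect as a departure from the pre-intervention course, here relative to the control arm. It needs enough pre-intervention points to fix the level and slope in each arm. If the analysis runs on the 2019-2021 window as written, fewer than 12 months precede the intervention. A trend fitted to so short a stretch is imprecise, and within one arm it cannot be told apart from season.

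The intervention and the pandemic also began within about 6 months of each other. The only period boundary with a date belongs to the pandemic. A plan that leaves the intervention break undated, and gives conflicting data windows, allows the baseline and break to be settled after the primary results are known. The baseline matters more than usual here because the intervention sites were selected for below-average performance (Eligibility Criteria and Recruitment of Facilities). A short run-in gives little protection against regression to the mean.

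**Working it through.** **Step 1. Reproduce the stated figure.** September 2019 to March 2020 is 6 elapsed months, which matches the article's approximately 6 months. The September start is therefore consistent with the dose-recording date.

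**Step 2. Count months.** January 2019 to March 2020 is 15 months. Late 2019 is read as October to December.

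| Start | Pre-intervention months from Jan 2019 | Full pre-intervention quarters from 2019 | Pre-intervention months from Jan 2017 | Intervention months inside the 15 |
|---|---|---|---|---|
| Sep 2019 | 8 | 2 | 32 | 7 |
| Oct 2019 | 9 | 3 | 33 | 6 |
| Nov 2019 | 10 | 3 | 34 | 5 |
| Dec 2019 | 11 | 3 | 35 | 4 |

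The quarter count matters only if Table 1 means quarterly data rather than a quarterly extraction schedule; the wording allows either.

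**Step 3. Precision of the pre-intervention slope in one arm.** For n equally spaced months with independent errors of standard deviation σ, SE(slope) = σ / √[n(n² − 1)/12].

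- n = 8: 8 × 63/12 = 42, so SE = 0.154σ per month.
- n = 32: 32 × 1023/12 = 2728, so SE = 0.019σ per month.
- Ratio: √(42/2728) = 0.12.
- For a December start (11 against 35 months): √(110/3570) = 0.18.

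**Step 4. Precision of the between-arm effect.** The model is a two-arm segmented regression with intercept, time, level change and slope change at the intervention start, each interacted with arm. A second version adds level and slope changes at April 2020, also interacted with arm. Standard errors are the square roots of the diagonal of (X′X)⁻¹, in units of σ. The table is for a September 2019 start.

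| Model | Series | SE, level change | Ratio | SE, slope change | Ratio |
|---|---|---|---|---|---|
| One break | 2019-2021 | 1.219 | 1 | 0.221 | 1 |
| One break | 2017-2021 | 0.730 | 0.60 | 0.043 | 0.19 |
| One break | 2017-2022 | 0.674 | 0.55 | 0.033 | 0.15 |
| Two breaks | 2019-2021 | 1.464 | 1 | 0.345 | 1 |
| Two breaks | 2017-2021 | 1.091 | 0.75 | 0.269 | 0.78 |
| Two breaks | 2017-2022 | 1.091 | 0.75 | 0.269 | 0.78 |

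For a December 2019 start, the same calculation for 2017-2021 against 2019-2021 gives level-change ratios of 0.735/1.067 = 0.69 (one break) and 1.280/1.495 = 0.86 (two breaks). The slope-change ratio with two breaks is 0.633/0.647 = 0.98, because only 4 months then lie between the breaks.

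**What this shows.** The gain comes from 2017-2018. With a separate pandemic break, 2022 adds nothing to the precision of the change at the intervention start; it informs only the arm contrast after April 2020.

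**The case against.** **The April 2020 split is about COVID-19.** A reader might infer that the plan counts intervention months as untreated in the intervention effect, and so dilutes it towards the null. The document does not support that. It labels the two periods by the pandemic. The Abstract describes a first analysis that ignores allocation, to gauge the pandemic's effect, and the Discussion defers stratification by arm to later work. The arm comparison is described separately, with no date for its interruption. This objection stands in full, and no dilution figure can be attributed to the plan.

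**The 2017-2018 years may enter the model.** They are named as the baseline period, and nothing excludes them. That is fair, and the count of 8 is conditional on it. But Study Design states the analysis window as 2019 to 2021, and the promise to provide the baseline does not override that. The text points two ways.

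**Break dates and series length belong in the full protocol or analysis plan.** Their absence alone would be no finding. Conflicting start dates and data windows within the article are another matter.

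**The control arm removes shared seasonality.** It does, to the extent that the arms share it. The difference between the arms in pre-intervention trend still rests on 8 to 11 points per arm.

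**The data may not be in hand.** Table 1 starts in 2019, so availability of the earlier years is not certain. This stands as a condition on the cost.

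**Conclusion.** The concern holds in limited form. On the window stated in Study Design, the primary mortality analysis has 8 pre-intervention months with a September 2019 start, or 9 to 11 with a late-2019 start. That is too few for a dependable pre-intervention trend or a seasonal pattern. The dated split mixes 8 to 11 untreated months with 4 to 7 intervention months, so it must not become the intervention contrast; the article does not say that it will.

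Using 2017-2018 gives 32 to 35 pre-intervention months. The standard error of the between-arm level change falls to about 0.60 to 0.69 of its value with one break, and to 0.75 to 0.86 with a separate pandemic break. These ratios are illustrative. They assume independent monthly points of equal variance and linear trends within segments. Autocorrelation, overdispersion and the small number of maternal deaths would change them. They do not show that the analysis would be adequately powered after the change.

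**What to change.** 1. State one intervention start date and use it in the Abstract, Intervention Dose and Discussion.
2. State one data window and one data interval, and align Study Design, Data Sources (text and Table 1) and Statistical Analysis, Objective 1.
3. State that 2017-2018 enters the interrupted time series model as monthly data for both arms, with 2022 as well if it was extracted as Data Sources reports.
4. Place the intervention break at the reconciled start date, with a separate arm-interacted break at April 2020 for the pandemic.
5. Keep the comparison of January 2019-March 2020 with April 2020-March 2021 for describing COVID-19, and say that it is not the intervention contrast.

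If the 2017-2022 extraction is correct and monthly facility data are available, the cost is wording and model code. If Table 1 is correct, a further extraction for 2017-2018 is needed.
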